### **5.3. Exclusion criteria**

Participants fulfilling any of the following criteria are not eligible for inclusion in this study

- Active tuberculosis, or history of taking anti-tuberculosis medications within 12 months prior to screening
- any *Loa loa microfilaria* infection detected by microscopy
- AST/ALT > 2x the upper limit of normal range (ULN)
- Taking an experimental drug in the last 4 weeks
- Antimalarial treatment in the last 4 weeks
- Use of systemic antibiotics with known antimalarial activity within 30 days of study enrolment (e.g. trimethoprim-sulfamethoxazole, doxycycline, tetracycline, clindamycin, erythromycin, fluoroquinolones, or azithromycin).
- Use of ivermectin within 30 days of study enrolment
- Participants taking herbal medication within one week of screening
- Known or suspected electrolyte imbalance, e.g. hypokalaemia, hypocalcaemia or hypomagnesaemia with clinical significance
- Moderate to severe anaemia (Haemoglobin level <8 g/dL)
- Any confirmed or suspected immunosuppressive or immunodeficient condition, including human immunodeficiency virus (HIV) infection
- Severe malnutrition (Body Mass Index (BMI) < 16.0)
- Pregnant or nursing (lactating) women
- Known chronic underlying disease such as sickle cell disease or severe cardiac impairment
- Participants with serum creatinine  $\geq 2 \times$  ULN in the absence of dehydration. In case of dehydration, Participants with serum creatinine  $\geq 2 \times$  ULN after oral or parenteral rehydration
- Participants with any psychiatric or neurological condition including substance abuse
- Allergy to ivermectin

### **5.4. Recruitment and Informed Consent**

All participants will sign and date the informed consent form before any study specific procedure is performed. At the screening visit, the participant will be fully informed of all aspects of

the trial, the potential risks and their obligations. The following general principles will be emphasized:

- Participation in the study is entirely voluntary
- Refusal to participate involves no penalty or loss of medical benefits
- The participant may withdraw from the study at any time
- The participant is free to ask questions at any time to allow him or her to understand the purpose of the study and the procedures involved

The aims of the study and all tests to be carried out will be explained. The participant will be given the opportunity to ask about the details of the trial and will then have sufficient time to consider whether or not to participate. Participants will be asked to sign and date two copies of the consent form, one which will belong to them to keep, and one to be stored in the Investigator's File. These forms will also be signed and dated by the Investigator.

### **5.5. Withdrawal of Participants**

In accordance with the principles of the current revision of the Declaration of Helsinki (updated 2013) and any other applicable regulations, a participant has the right to withdraw from the study at any time and for any reason and is not obliged to give his or her reasons for doing so. The Investigator may withdraw the participant at any time in the interests of the participant's health and well-being. In addition, the participant may withdraw/be withdrawn for any of the following reasons:

- Investigator decision
- An AE, which requires discontinuation of the study involvement or results in inability to continue to comply with study procedures

The reason for withdrawal will be recorded in the CRF. If withdrawal is due to an AE, appropriate follow-up visits or medical care will be arranged, with the agreement of the participant, until the AE has resolved, stabilized or a non-trial related causality has been assigned. Any participant who is withdrawn from the study may be replaced, if that is possible within the specified time frame.

If a participant withdraws from the study, blood samples collected before their withdrawal from the trial will be used/ stored unless the participant specifically requests otherwise. The samples may be destroyed if the participant did not agree to have their samples stored.

## 6. Study procedures

### 6.1. Screening visit

Once the informed consent is signed, the following screening procedures will be undertaken:

- Full medical history
- Prior concomitant medication
- Demographic data (gender, age)
- Clinical examination (including measurement of height and weight)
- Vital signs (including pulse, blood pressure and body temperature)
- Pregnancy test in female participants of childbearing potential (18 – 49 years)
- Biochemistry tests: AST, ALT and creatinine,
- Haematology: full blood count and WBC differential blood count
- Malaria blood film for parasite count and species as well as identification of *Loa loa*
- Blood sampling for qPCR

AEs will be recorded from the signature of the informed consent. Abnormal clinical findings from the medical history, vital signs assessment or blood tests at any point in the study will be assessed using established reference intervals of the laboratory. If an abnormal finding is deemed to be clinically significant, the participant will be informed, and appropriate medical care arranged with the permission of the participant.

### 6.2. Treatment

#### 6.2.1. Treatment arms

Participants fulfilling all inclusion criteria and none of the exclusion criteria will be assigned sequentially to receive ivermectin 200 µg/kg orally single dose for one (5 first subjects), two or three days (10 next available subjects). Following interim safety analysis, 34 subjects will be randomly allocated in two treatment arms to receive either 300 µg/kg per day for 3 days or placebo for 3 days. There will be four consecutive study arms (arms IV a) and b) will be parallel):

- Arm I: 5 participants (200 µg/kg single dose)
- Arm II: 5 participants (2x200 µg/kg)

- Arm III: 5 participants (3x200 µg/kg)
- Arm IV:
  - a) 17 participants (3x300 µg/kg)
  - b) 17 participants (placebo-control)

#### 6.2.2. Randomization of treatment

As Arms I-III serves descriptive purposes for safety assessment of the study drug, there will be no randomization.

Participants for Arm IV will be randomized to arm IVa or arm IV b through a randomization system prior to the first treatment. The randomization ratio will be 1:1 (3-day treatment, control group). A dedicated member of the team, who is not involved in volunteer management or diagnostic activities, will keep the randomization envelopes and dosing schedule. A third party outside the study team and sponsor will generate and distribute the randomization list and sealed envelopes using a random number generator.

A sealed envelope containing the participants arm will be used for randomization in the study and the randomization data are kept strictly confidential until formal interim safety review or the final analysis. At the time of final analysis, the allocation data will be loaded into the statistical programming system for access to trial statisticians and pharmacokinetics.

#### 6.2.3. Blinding and treatment procedure

One none-blinded person will prepare the treatment assigned by the randomization system, verify that the Participant's treatment group is assigned by the envelope and complete the corresponding treatment record form. Only the person administering ivermectin and placebo would know the groups allocation. Ivermectin and placebo are similar but not identical and will be administered to each participant separately out of the original packaging without changing the labels. All other study personnel (e.g. physicians, microscopists) and study participants will be unaware of the group allocation.

The study drugs will be administered under supervision with a fat containing food such as a croissant with bread spread. These two persons (the person administering the drug and the supervising person) are not otherwise involved in the conduct of the trial. The first dose will be administered at the time of the participant's recruitment into the study. Time between the blood film preparation and treatment administration will be no longer than four hours. Subsequent doses will be given at twenty-four hourly intervals, food will be provided together with the investigational drug.

In the event of vomiting/spitting within one hour of ingestion, the same dose of drug will be re-administered from a supplemental drug supply. However, re-dosing will be done only once per day of treatment administration.

All study treatment taken must be recorded in the CRF, along with any comments about whether the Participants swallowed all or part of the medication.

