| Study design                             | Single-centre, open label and double-blinded, randomized, placebo-controlled dose escalation trial with two stages                                                                                                                                                                                                                                                                                                                                                                                                                                                                                                                                                                                                                                                                                                                                                                                                                                                                                                                                                                                                                                                                                                                                                                                                                                                                                                                                      |

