## 4. Trial design

### 4.1. Trial overview

The study is designed as a dose escalation trial with who stapes to assess the safety and efficacy of ivermectin on the reduction of *P. falciparum* parasitaemia in asymptomatic participants in

an endemic area of Gabon. The first stage is an open label trial and included arms I-III. The next stage is a randomized double-blind controlled trial. Potential adult participants living in Lambaréné and in the Tsamba-Magotsi Department, Gabon will be screened for parasitaemia of 200 to 5000 *P. falciparum* parasites/ $\mu$ l without clinical signs of malaria for inclusion in the clinical trial. Participants will be included sequentially in arms I-IV with a pause between arms to allow safety review by DSMB. Each dose escalation stage will only commence after safety assessment of the previous stage and approval by the Data and Safety Monitoring Board. The sponsor can, in consultation with the DSMB, suspend recruitment at any time based on safety considerations.

Study arms:

- Arm I: 5 participants (200  $\mu$ g/kg single dose)
- Arm II: 5 participants (2x200  $\mu$ g/kg)
- Arm III: 5 participants (3x200  $\mu$ g/kg)
- Arm IV:
  - a) 17 participants (3x300  $\mu$ g/kg)
  - b) 17 participants (placebo-control)

All participants will be hospitalized for three days. Assessment during treatment period and follow-up visit will be the same in all study arms.

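### Arm IV is called double-blind, but section 6.2.3 doses non-identical products from their original, unchanged packs and describes no step that hides product or label from the participant

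*Protocol*

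**What the plan says.** The synopsis describes the trial as an "open label and double-blinded, randomized, placebo-controlled dose escalation trial" with two stages. Section 4.1 assigns the blinding to the second stage: "The next stage is a randomized double-blind controlled trial".

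Section 6.2.3 sets the dosing procedure. On the products: "Ivermectin and placebo are similar but not identical and will be administered to each participant separately out of the original packaging", with the labels left unchanged. On who knows: "Only the person administering ivermectin and placebo would know the groups allocation". On who does not: "All other study personnel (e.g. physicians, microscopists) and study participants will be unaware of the group allocation".

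The same section has one unblinded person prepare the assigned treatment, has each dose taken under supervision with food, and keeps the administering and supervising persons out of the rest of the trial.

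Section 6.2.2 gives the envelopes and dosing schedule to a team member who has no part in managing volunteers or in diagnostics. A third party outside the study team and sponsor generates the list. The section adds that "randomization data are kept strictly confidential until formal interim safety review or the final analysis".

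**The concern.** An original pack with its own label would normally identify the product to anyone who sees it. A procedure that doses from such packs, with products that differ, needs a concealment step before participants can be called blinded. Section 6.2.3 has none. This is not a detail that an analysis plan could supply later, because the protocol itself fixes a method that does not support its own statement about participants.

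The outcomes that depend on the participant's state of knowledge are at stake:

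- Adverse events include those the participant reports (section 12.3), and they feed the secondary safety endpoint (8.4).
- The primary safety endpoint counts related events (8.3). Relatedness rests on the investigator's clinical judgement (12.2) and also enters the safety-hold criteria (12.6).
- Participants may withdraw at any time (5.5), and those lost to follow-up are replaced to reach 49 evaluable (5.1). Dropout driven by knowledge of allocation could therefore change who is analysed for efficacy.

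**Working it through.** No figure in the protocol depends on the blinding, so the check is a comparison of the passages. The sample-size inputs (25% versus 75%, one-sided 2.5%, 90% power, 17 events) are untouched by how tablets are dispensed.

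**Step 1. What participant blinding would need.** Either the products match, or the differences and labels are kept from the participant.

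| Possible measure | Section 6.2.3 |
|---|---|
| Matching products | No: similar, not identical |
| Neutral or relabelled packs | No: original packs, labels unchanged |
| Over-encapsulation or opaque container | Not described |
| Product prepared or handed over out of sight | Not described |
| Participants dosed separately | Yes |

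Only the last row is met. Separate dosing stops side-by-side comparison. It does not hide a label or a tablet from the person taking it.

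**Step 2. Which feature matters more.** A participant sees only one product throughout, so a difference in tablet appearance alone tells them little without a reference. The label can identify the product directly. The weak point is therefore mainly the unchanged pack, with the non-identical tablets second.

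**Step 3. Number of exposures.** Section 4.1 gives 17 + 17 = 34 participants in Arm IV. The schedule in section 7 gives doses at 0, 24 and 48 hours, so 34 × 3 = 102 planned dosing occasions, 51 per arm. A repeat dose after vomiting would add to this.

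**Step 4. Which outcomes this reaches.**

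- Primary efficacy (8.1) is read by microscopists stated to be blinded. A participant's knowledge does not alter a slide count directly.
- Participant-reported events and withdrawal are reached in one step, from the participant's own knowledge.
- Relatedness is reached in two steps: the participant learns the allocation, then tells a blinded physician. A stay of at least 72 hours (section 9) gives room for that.

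**Step 5. Who is listed as knowing.** The section calls the preparer unblinded, then says that only the person administering knows. The supervising person watches dosing from labelled packs and is not listed as unblinded. The envelope keeper in 6.2.2 is not mentioned in this context either. The list of people who may know is incomplete as worded.

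**The case against.** The strongest reply is that the protocol does not say a participant ever sees the pack, and states outright that participants will be unaware. The unblinded person may already take the tablets out elsewhere. That is fair, and it limits the claim: the document shows an unsecured blind, not a broken one. It does not remove the point, because the text gives no step by which the stated result is achieved.

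Four stronger readings may occur to a reader, and the documents do not support them.

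- **Participants compare tablets on the ward.** Doses are given separately and taken under supervision with food. Nothing suggests that tablets are kept, so at most participants could compare recollections of similar-looking products.
- **The preparer's or supervisor's knowledge biases the trial.** The preparer is already called unblinded. The administering and supervising persons have no other role in the trial. Only the wording needs tidying.
- **Interim review releases the Arm IV allocation.** The scheduled reviews fall between arms (4.1), and section 6.2.1 places the interim safety analysis before the 34 are randomised. Arms I to III are not randomised, so at those reviews there is no Arm IV allocation to release. The clause in 6.2.2 could matter only for an unscheduled review during Arm IV, and it does not say who would receive the data.
- **Outcome assessors are unblinded.** Physicians and microscopists are stated to be blinded. Any effect on them needs leakage from the participant.

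The prohibition of other antimalarials, the request to avoid herbal remedies and the recording of concomitant medication (6.2.4, 6.2.5) also limit how far a participant's behaviour could affect parasitaemia.

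**Conclusion.** The point holds in limited form. Section 6.2.3 fixes a dosing method that does not secure the participant blinding it asserts, and the double-blind label in the synopsis and 4.1 goes further than the procedure supports. As written, the procedure supports blinding of assessors and clinical staff.

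The gap covers all 34 Arm IV participants and 102 planned dosing occasions. Participant-reported adverse events and withdrawal are the main exposure, relatedness is a secondary one through leakage, and the microscopy endpoint is largely protected. The size of any bias cannot be computed from the document.

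This rests on two assumptions: that the original labels distinguish ivermectin from placebo, and that no concealment step is applied beyond those the protocol describes. If a step exists in an SOP, stating it in the protocol settles the label question; the non-identical tablets would still need to be addressed.

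**What to change.** In section 6.2.3, state that the unblinded person removes the tablets from the pack out of the participant's sight and hands them over in a plain opaque container. If the products can still be told apart, describe Arm IV as observer-blind in the synopsis and in section 4.1.

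Three wording edits go with this:

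- In 6.2.3, list the supervising person and the envelope keeper among those who may know the allocation, alongside the preparer and the person administering. The outside party who generates the list is already covered by 6.2.2.
- In 6.2.2, state that any release of allocation before the final analysis goes only to the DSMB.
- Make emergency unblinding under section 12.4 an explicit exception, so that the restriction does not contradict it.

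The cost is opaque containers, minor SOP work and possibly a weaker blinding label. Dose, schedule and sample size are unaffected.

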#### 6.2.4. Concomitants medication

All medication (other than the investigational drugs) and significant non-drug therapies administered after the Participant starts treatment with study drug will be documented on the concomitant medication.

#### 6.2.5. Prohibited medication

The use of the following treatments is NOT allowed

- Antimalarials other than the study drug and rescue medication (Artemether/lumefantrine) are not permitted during the entire study period.
- Herbal medication should not have been taken within 1 week before the study treatment is given and should be avoided until the last study visit

As ivermectin is metabolized by Cytochrome P450 3A4 (abbreviated CYP3A4), especially substances which could alter Cyp3A4 activity should be avoided before and after intake of ivermectin. This includes substrates as well as inhibitors and inducers of Cyp3A4. Only participants willing to avoid the intake of these substances before and after administration of ivermectin will be enrolled in the study.

#### 6.2.6. Rescue medication

The following circumstances warrant discontinuation of study treatment and the implementation of rescue medication

- Any parasitaemia based on microscopy with fever ( $>38.5^{\circ}\text{C}$ , observed by study team) post-dose
- Development of danger signs or severe malaria on any treatment day between Study Day 0 and Day 7 in the presence of parasitaemia
- Parasitaemia  $\geq 20,000$  parasites/ $\mu\text{l}$

The start of the rescue medication with artemether-lumefantrine may occur after the start of trial medications and up to Study Day 7 as deemed necessary by the investigator. Any

participants who would not need the rescue medication up to study Day 7, will be given artemether-lumefantrine at end of active follow-up (Day 7). The rescue medication according to the local guidance will be used to treat severe malaria.

## **7. Routine assessment**

All clinical visits and procedures will be undertaken by one investigator of the clinical team. The procedures to be included in each visit are documented in Table 1. Each procedure is assigned a time point and a window period of  $\pm 4$  hours within which the review will be conducted. Participants have to be seen at all visits on the designated day, or as close to it as possible.

| Treatment day                                                                                      |           | 0 |   |    | 1  |    |    | 2  |    |    | 3  | 4  | 5   | 6 | 7 | 14 |
|----------------------------------------------------------------------------------------------------|-----------|---|---|----|----|----|----|----|----|----|----|----|-----|---|---|----|
| Time (hours) after first dose                                                                      | Screening | 0 | 8 | 16 | 24 | 32 | 40 | 48 | 56 | 64 | 72 | 96 | 120 |   |   |    |
| Informed consent                                                                                   | X         |   |   |    |    |    |    |    |    |    |    |    |     |   |   |    |
| Inclusion/ exclusion criteria                                                                      | X         |   |   |    |    |    |    |    |    |    |    |    |     |   |   |    |
| Demography, medical history                                                                        | X         |   |   |    |    |    |    |    |    |    |    |    |     |   |   |    |
| Haematology and biochemistry                                                                       | X         |   |   |    |    |    |    |    |    |    | X  |    | X   |   | X | X  |
| Asexual & gametocyte parasite count (thick & thin blood films)                                     | X         | X | X | X  | X  | X  | X  | X  | X  | X  | X  | X  | X   | X | X | X  |
| Blood in RNA later (for qPCR)                                                                      | X         | X | X | X  | X  | X  | X  | X  | X  | X  | X  | X  | X   | X | X | X  |
| Blood for membrane feeding

*4 hours after last ivermectin treatment together with PK sample | X         |   |   |    |    |    |    |    | X* |    | X  |    |     |   | X | X  |
| Stool sample                                                                                       | X         |   |   |    |    |    |    |    |    |    | X  |    |     |   | X |    |
| Vital signs + temperature                                                                          | X         | X | X | X  | X  | X  | X  | X  | X  | X  | X  | X  | X   | X | X | X  |
| Physical exam                                                                                      | X         | X |   |    | X  |    |    | X  |    |    | X  | X  | X   | X | X | X  |
| Dosing                                                                                             |           | X |   |    | X  |    |    | X  |    |    |    |    |     |   |   |    |
| PK                                                                                                 |           | X | X | X  | X  | X  | X  | X  | X  | X  | X  | X  | X   | X | X | X  |

|                                  |   |   |   |   |   |   |   |   |   |   |   |   |   |   |   |   |
|----------------------------------|---|---|---|---|---|---|---|---|---|---|---|---|---|---|---|---|
| Prior and concomitant medication | X | X | X | X | X | X | X | X | X | X | X | X | X | X | X | X |
| AEs                              | X | X | X | X | X | X | X | X | X | X | X | X | X | X | X | X |

